**Dose determination for Phase 2b**

The evaluation of safety and pharmacokinetic parameters in both dosing groups will guide the choice for the dose to be used in the Phase 2b study. This dose will range between 0,5 and 2 mg/kg given in a single administration. Alternatively, a corresponding flat dose might be considered.

Based on good safety and tolerability of phase 2a and PK data with the higher dose, a single infusion of 2 mg/kg of Xav-19 was selected for phase 2b.

Furthermore, a corresponding flat dose regimen (fixed dose of 150mg XAV-19) will be assessed in the terminal ancillary open study which will be performed on 20 patients. This regimen is based on:

- The preclinical data acquired during the development of XAV-19 compared to the phase 2a data: indeed, a XAV-19 concentration of approximatively 1 to 5 μg/ml is required to fully neutralize all variants (Wuhan, British and South-African forms)^23^. The Phase 2a has demonstrated that a single intravenous perfusion of XAV-19 at 2 mg/kg was safe, achieving a median serum Cmax of 50.4 μg/ml and D8 concentration of 20.3 μg/ml with an elimination half-life (T1/2) estimated at 11.4 days (Gaborit B et al MedRxIV, 2021, article in progress). All this data indicate that XAV-19 can provide high and sustained therapeutic activity with an inhibitory quotient well above 10.
- The phase 2a clinical data: based on patients’ median weight which was 77.3 Kg ([72-98] range from 52 to 120), a fixed dose of 150mg of XAV-19 will therefore be equivalent to a median dose of 1.94 mg/Kg; ([2.08-1.53 Kg]; Range 2.88-1.36*) (*to note, above 110 Kg, blood volume no longer increases proportionally to mass). If we consider 2 extremes body weights: a fixed dose of 150 mg in a 50 kg patient corresponds to a dose of 3 mg/Kg, a dose that theoretically results in a Cmax of 75 µg of XAV-19 per ml of plasma; a fixed dose of 150 mg in a 120 kg patient corresponds to a dose of 1.25 mg/Kg resulting in a Cmax of approximately 30 µg of XAV-19 per ml of plasma. These two extreme cases show that the therapeutic index will remain high, varying from 6 to 15 times the neutralizing concentration. The therapeutic window is therefore wide with XAV-19. These examples also show that there will be no exposure above the upper limit of 40 mg/Kg, a dose that has been administered in humans without any product-related adverse events being noted (data extrapolated from the ongoing LIS1 trial where another GH-pAb is administered; NCT 04431219).

Furthermore, initial volume of distribution and clearance data from phase 2a suggest that the intensity of diffusion of XAV-19 in the body does not increase with patient weight and the rate of elimination of XAV-19 from the blood does not increase ( or decrease ) with patient weight (Gaborit B et al MedRxIV, 2021, article in progress).

- Lastly, the literature indicates that for therapeutic Abs, in contrast to the conventional assumption, body weight-based dosing does not always offer advantages over fixed dosing in reducing exposure variability.^24^

These data lead us to investigate a fixed dose of XAV -19 for comparison with conventional weight adjusted dose as tested so far in the phase 2b patients.

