### Terminal ancillary Study (20 additional patients)

#### Objective

The objectives are:

-to compare pharmacokinetic parameters in patients receiving a fixed dose of 150mg with patients receiving 2mg/Kg of XAV-19 (master phase 2b), in order to confirm that the exposure and variability are similar

-to compare the effects of neutralizing antibodies use on virus-induced immune response on longitudinal follow-up, and targets for "immuno-monitoring"

-to investigate the immunogenicity of COVID-19 during treatment with XAV19 in patients receiving a fixed dose of 150mg with patients receiving 2mg/Kg of XAV-19

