### Statistical justification of the number of inclusions

Phase 2 a:

As it is a Phase 2 a, the number of patients was determined according to relevant publications of phase 2a. It was decided to enrol two cohorts of 8 patients (6 treated patients and 2 matching placebo in each cohort).

Phase 2 b:

Assuming a true treatment diminution in clinical failure rate of 10% for XAV-19 added to SoC therapy compared to placebo added to SoC therapy where a rate of 20% is expected, a sample size of 398 randomized participants provides at least 80% power that the primary analysis will be statistically significant at the two-sided 5% significance level.

The 20 patients of the open-label ancillary terminal study (150 mg dose of XAV-19) will not be included in the primary analysis. Their pharmacokinetic characteristics and variability will be compared to the parameters of randomized phase 2b patients taking part in the ancillary pharmacokinetics ancillary study and immunomonitoring ancillary study.

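### The flat-dose rationale rests on two different weight assumptions, and the planned comparison of group exposure and variability is a weak way to tell them apart; a prespecified regression on weight should be added.

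*Combined protocol and SAP*

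**What the plan says.** Protocol section 1.3 (Dose determination for Phase 2b) states that "a single infusion of 2 mg/kg of Xav-19 was selected for phase 2b" and that "a corresponding flat dose regimen (fixed dose of 150mg XAV-19) will be assessed in the terminal ancillary open study". It converts the flat dose to mg/kg at the phase 2a weights ("a fixed dose of 150mg of XAV-19 will therefore be equivalent to a median dose of 1.94 mg/Kg"). It then takes two extremes. At 50 kg, 150 mg is 3 mg/kg with a theoretical Cmax of 75 µg/mL. At the other end, "a fixed dose of 150 mg in a 120 kg patient corresponds to a dose of 1.25 mg/Kg resulting in a Cmax" of about 30 µg/mL. From these it derives a therapeutic index of 6 to 15.

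The next paragraph of the same section says that initial phase 2a volume and clearance data "suggest that the intensity of diffusion of XAV-19 in the body does not increase with patient weight", and that elimination neither increases nor decreases with weight.

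Protocol section 3.2.3 sets the objective of comparing PK parameters between the two regimens "in order to confirm that the exposure and variability are similar". Section 7.2.2 repeats the plan: "Their pharmacokinetic characteristics and variability will be compared to the parameters of randomized phase 2b patients" in the PK and immunomonitoring ancillary studies. Neither section gives a test, a margin, a precision target or an analysis by weight. The SAP specifies no PK analysis.

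**The concern.** A Cmax that falls from 75 to about 30 µg/mL between 50 and 120 kg requires volume proportional to weight. If volume does not change with weight, 150 mg gives about the same Cmax at both weights. The therapeutic-index argument uses the first assumption, and the supporting argument for a fixed dose uses the second.

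The two assumptions also differ on which regimen spreads exposure more across patients, which is what a comparison of fixed with weight-adjusted dosing should clarify. Similar average exposure in the sub-study could be read as support for the flat dose at all weights. But 150 mg was chosen to match 2 mg/kg at the median weight, so similar averages are expected either way. Exposure at the light and heavy ends would remain unestimated, although weights and PK samples are collected.

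**Working it through.** **Inputs from the documents.** Flat dose 150 mg; comparator 2 mg/kg; phase 2a median weight 77.3 kg, interval 72-98, range 52-120; median Cmax 50.4 µg/mL at 2 mg/kg (all section 1.3). 20 flat-dose patients; 90 patients in the PK study (section 3.2); 1:1 randomisation.

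**Assumptions.** 72-98 kg is an interquartile range and weight is log-normal, so SD of log weight = ln(98/72)/1.349 = 0.229. The comparator group is 45 patients (half of 90). Residual log-SD of exposure is not in the documents; 0.3 is used, with 0.2 to 0.4 as the range.

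**Reproducing the plan's figures.** 150/77.3 = 1.94 mg/kg; 150/72 = 2.08; 150/98 = 1.53; 150/52 = 2.88. The stated lower end, 1.36, is 150/110, in line with the footnote on blood volume above 110 kg; the 120 kg example uses 150/120 = 1.25. Cmax per mg/kg is 50.4/2 = 25.2, so 3 × 25.2 = 75.6 and 1.25 × 25.2 = 31.5 µg/mL. The plan's 75 and about 30 follow from proportional scaling.

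**Under weight-independent volume.** V = 2 × 77.3/50.4 = 3.07 L. Then 150 mg gives 150/3.07 = about 49 µg/mL at both 50 and 120 kg, while 2 mg/kg gives 100/3.07 = about 33 and 240/3.07 = about 78 µg/mL. The spread moves from the flat regimen to the weight-based one.

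**Means.** Let V or CL = k × W^b. Flat exposure is proportional to 150/W^b and weight-based exposure to 2W/W^b. With the same weight distribution in both groups, W^b cancels:

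geometric mean ratio = 150/(2 × geometric mean weight) = 75/77.3 = 0.970 for b = 0, 0.5 and 1.

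If the typical weight were 84 kg (geometric midpoint of 72 and 98), the ratio is 75/84 = 0.89, again for every b. Arithmetic means differ slightly: 0.945 at b = 0 and 0.996 at b = 1.

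**Variability.** Log-variance is b² × 0.229² + residual² on the flat dose and (1−b)² × 0.229² + residual² on 2 mg/kg. At residual 0.3 and b = 1 the flat/weight-based ratio is (0.0522 + 0.09)/0.09 = 1.58; at b = 0 it is the inverse, 0.63. At b = 0.5 it is 1. Two-sided 5% F-test, 20 against 45:

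| Residual log-SD | Variance ratio, b = 0 / b = 1 | F-test power, b = 0 / b = 1 | Observed direction correct, b = 0 / b = 1 |
|---|---|---|---|
| 0.2 | 0.43 / 2.31 | 52% / 60% | 99% / 97% |
| 0.3 | 0.63 / 1.58 | 19% / 23% | 89% / 86% |
| 0.4 | 0.75 / 1.33 | 10% / 12% | 78% / 74% |

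Simulation at 0.3 gives 19% and 24%.

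**Pooled regression.** The slope of log(exposure/dose) on log weight is −b. With 65 patients, SE = 0.3/(0.229 × √64) = 0.164, or about 0.17 allowing for sampled weights; the range is 0.11 (residual 0.2) to 0.22 (residual 0.4). An exponent of 1 is then separated from 0 in 99% or more of sub-studies. If the true exponent is 0.5, power to reject either extreme is about 84% at residual 0.3 and 61% at 0.4.

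**The case against.** **Variability is part of the plan.** A reader might infer that the sub-study cannot test the weight assumption at all. The documents do not support that. Sections 3.2.3 and 7.2.2 both name variability, and the variance ratio reverses between the two assumptions. Its observed direction would be right in about 86 to 89% of sub-studies at residual 0.3, and with low residual variability (0.15) F-test power reaches 84 to 87%. What stands against the plan is low power over most of the plausible range and the absence of a criterion.

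**The stated objective is similarity, not a weight exponent.** This is correct, and for that objective the average comparison is relevant. It should stay. But in this model equal variability is expected only near b = 0.5, which matches neither paragraph of section 1.3.

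**The ratio of 0.97 is not fixed by design.** It needs similar weights in both groups, and the 20 patients come later, open label and without randomisation. With geometric mean weights of 72 kg (flat) and 84 kg (weight-based), the ratio is 150/168 = 0.89 at b = 0 and (150/72)/2 = 1.04 at b = 1. This limits the claim, and it also argues for adjusting for weight.

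**Other sections might already cover it.** Section 3.2 says the analyses will be identical to those of phase 2a. The phase 2a PK models in section 7.2.1 are ANOVA models with subject and day terms; they contain no weight term.

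**The two paragraphs may not strictly exclude each other.** The Cmax figures are labelled theoretical extremes, the phase 2a statement is tentative, and its term for diffusion is undefined (read here as volume, as the sentence's own opening suggests). A reader might conclude that one paragraph is simply false; the text does not settle which. It does show that they use different assumptions without saying so.

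**Conclusion.** The point holds in limited form. The two paragraphs of section 1.3 use opposite weight assumptions and must be reconciled. With similar weights in the two groups, the comparison of average exposure is uninformative on weight scaling. The variability comparison is informative in direction but weak, and no criterion is stated for it. No weight-covariate PK analysis is planned.

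The power figures rest on the assumed residual log-SD, the interquartile reading of 72-98 kg in a small phase 2a sample, and 45 comparators. The comparator number could be larger, because section 7.2.2 also draws on the immunomonitoring study.

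The consequence is modest. The 20 patients are outside the primary analysis, so no main efficacy conclusion depends on this. It is an improvement at almost no cost to a sub-study whose purpose is to compare the two regimens.

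**What to change.** 1. Reconcile the two paragraphs of protocol section 1.3: state which weight assumption underlies the Cmax predictions and the 6 to 15 index, and how it relates to the phase 2a volume and clearance findings.

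2. Keep the planned comparison of exposure and variability, and state in advance how similarity will be judged.

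3. Add to the ancillary analysis plan, before the sub-study data are analysed: a linear regression of log dose-normalised exposure (Cmax, Day 8 concentration, AUC), or of log volume and log clearance, on log weight, pooling the 150 mg and 2 mg/kg patients and using the actual dose given. Report the weight exponent with its 95% CI and the predicted exposure under each regimen over 52 to 120 kg. Present an interval that excludes neither 0 nor 1 as inconclusive. The model also adjusts for weight differences between the non-concurrent, non-randomised groups.

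The cost is about one paragraph of analysis plan and the edit to section 1.3. Weight is already recorded (section 6.3) and serial PK samples are already scheduled in both groups. No new patients or samples are needed, and no change of dose is proposed.

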**The bibliographical references are appended to the document.**

# Objectives and endpoints of Phase 2a

## Primary objective and endpoint

### Primary objective

The primary objectives of the study are to:

1. evaluate the Antibody titers of XAV-19 treated patients versus placebo treated patients at Day 8
2. assess the safety and tolerability of XAV-19.

### Primary endpoint

The primary endpoints are the:

1. pharmacokinetic measurement of the antibody titer of XAV-19 measurements of all treated patients and of all patients in the placebo group at Day 8
2. tolerability and adverse events of XAV-19 between the two groups of treated patients and vs. placebo over 29 days, evaluated as:

- Occurrence of all suspected XAV-19 related adverse effects and incidence of serious adverse events
- Proportion of participants with treatment emergent adverse events leading to study drug discontinuation
- Incidence of major or bacterial or fungal infections
- Incidence of hypersensitivity reactions and infusion reactions
- White cell count, hemoglobin, platelets, creatinine, ALT, AST, on D1, D3, D5, D8, D15 and D29
- SARS-CoV-2 viral load over time (D1-D29), as collected by nasopharyngeal swab samples
- Time to RT-PCR virus negativity in nasopharyngeal swab samples

## Secondary objectives and endpoints

### Secondary objectives

The secondary objectives of the study are:

1. To characterize pharmacokinetics (PK) of XAV-19 infected patients over the time from D1 to D29
2. To evaluate the Antibody titers of XAV-19 and to compare Group 1 treated patients versus Group 2 treated patients at Day 8.
3. To describe groups of patients according to clinical variables (Duration of supplemental oxygen, transfer in ICU, Normalization of fever, titer of Biomarkers, Ordinal scale assessed at Day 15, Hospital length of stay).

### Secondary endpoint(s)

The secondary endpoints are the:

1. Pharmacokinetic analysis: Antibody titer measurements at Day 1 (pre-dose, post-dose), Day 3, Day 5 (if applicable second XAV-19 administration): pre-dose and post-dose), Day 8, Day 15, and Day 29.
2. The antibody titer of XAV-19 measurements in Group 1 treated patients and Group 2 treated patients at Day 15.
3. Clinical aspects:

- Duration of supplemental oxygen
- Transfer to intensive care unit with need for invasive mechanical ventilation or high flow oxygen
- Normalization of fever ≥ 24 hours: clinical assessment every day from Day 1 to Day 14. Evaluation to be performed between 8 and 12 am, Day X evaluation will consider the higher value during Day X-1 (8 am to 8 am)

- Normal fever (≤ 37.8° C tympanic or ≤ 36.6°C axillary or ≤ 37.2°C oral taken 4 hours apart from antipyretic administration) each day and time to resolution of fever for at least 48 hours

- Biomarkers : CRP, Ferritin
- Ordinal scale assessed at Day 15. The 7-point ordinal scale is an assessment of the clinical status at the first assessment on day 15. The scale is as follows:

1. Not hospitalized, no limitations on activities;
2. Not hospitalized, limitations on activities;
3. Hospitalized, not requiring supplemental oxygen;
4. Hospitalized, requiring supplemental oxygen;
5. Hospitalized, on non-invasive ventilation or high flow O2 devices;
6. Hospitalized, on invasive mechanical ventilation or ECMO;
7. Death.

- Hospital length of stay

## Objective and endpoints for exploratory studies for phase 2a

Exploratory objectives will be to assess the effects of neutralizing antibodies use on virus-induced immune response on longitudinal follow-up, and to identify targets for "immuno-monitoring" for the next phase of the study and to investigate the immunogenicity of COVID-19 during treatment with XAV-19.

We will take advantage of the existing "Immunologie" research program” declared by Nantes CHU to set up the biocollection “POLYCOR”. This biocollection will be a biological and longitudinal follow-up of patients with diagnosis of COVID-19, to assess immune changes and host-virus interactions. Ethic authorization is already granted, and the preanalytical steps are already implemented and efficient. Blood samples (plasma, serum at -80°C, PBMCs) are stored in liquid nitrogen.

Blood samples taken will be stored in this biocollection until analyses.

Objectives of Collections of samples:

HD monitoring of circulating immune cells:

Two mAb panels validated by Cytek (https://cytekbio.com/pages/aurora#tab-data ) will be used for lymphocytes and MNP (mononuclear phagocytes) populations respectively.

1. Panel 1 - 35 Abs:

CD45RA/CD16/CCR5/CD11C/CD56/CD8/CCR7/CD123/CD161/IgD/CD3/CD20/IgM/IgG/CD28/CXCR3/CCR6/CXCR5/PD-1/CD141/CD57/CD14/CD45/CD11b/TCRgd/CD25/CD24/CD95/CXCR3/CD27/CD1c/CD127/HLA-DR/CD19/CD4/CD38.

1. Panel 2 -28 Abs:

CD40/CD16/CD56/CD3/CD86/CD45/CX3CR1/CD66b/CD85k/FCER1a/PD-L1/CD141/CD172a/CD14/CD11b/CD123/CD26/CD32/CD197/CD163/CD80/CD19/CD4/CD272/CD1c/CD11c/HLA-DR.

Both supervised and unsupervised analyses will be performed.

Serum cytokine/chemokine profiles in XAV19 vs. placebo COVID-19 pneumonia:

We will measure the concentration of MCP1, IP10, IL-10, IFNa, TNF-α, IL-1b, IL-6, IL-82 (in the phase 2a) and IL-6, IFNa2, IL-10, IP10, CCL2 (in the phase 2b).

Ex vivo pharmacodynamic:

Ability of patient serum to neutralize binding of recombinant SARS-CoV-2 Spike molecule to ACE-2 receptor in an ELISA format.

Description of transcriptomic analyses:

Messenger RNA molecules will be extracted from peripheral blood in order to identify transcripts that are specifically over- or under-expressed in correlation with the clinical status and with viral load. The goal is to identify possible biomarkers of the disease severity and disease responding to the treatment, and, using deconvolution bioanalyses, also identifying cell population changes in complement to the direct flow cytometry analyses. A focus will be made on B cell subpopulation and their role in interaction with Tfh cells.

# Objectives and endpoints of Phase 2b

## Primary objective and endpoint

### Primary objective

To evaluate the efficacy of XAV-19 + standard-of-care (Soc) therapy compared with placebo

+ Soc therapy for treatment of COVID-19 assessed by the proportion of patients who die or develop respiratory failure between baseline and Day 15.

### Primary endpoint

Patients who died or develop respiratory failure, as defined by the requirement of noninvasive ventilation, high-flow oxygen devices, invasive mechanical ventilation (corresponding to a score of 5 or more on the WHO 8 point ordinal scale) or by an increase of the required O2 supplement more or equals to 10 L/minutes with a non-rebreather mask (oxygen mask with reservoir bag).

## Secondary objectives and endpoints

### Secondary objectives

**The key secondary objectives** are to evaluate the efficacy of XAV-19 + standard-of-care (Soc) therapy compared with placebo + Soc therapy for treatment of COVID-19 between baseline and Day 8, and then between baseline and Day 29.

**The others secondary objectives** are to evaluate clinical efficacy and safety of the investigational therapeutic compared to the control arm, assessed by:

**Clinical severity**:

a) National Early Warning Score (NEWS) over 29 days:

*-* Change from baseline to Day 3, 5, 8, 15 and 29

- Time to discharge or a NEWS <=2 and maintained for 24 hours

b) 8-point ordinal scale over 29 days

- Time to improvement of one category from baseline (Day 1)

- Mean change in ordinal scale from baseline to Day 3, 5, 8, 15 and 29

- Percentage of subjects reporting each severity rating on an 8-point ordinal scale at Day15

c) Improvement of clinical and biological parameters over Day 15

d) Oxygenation

- Duration of oxygen therapy over 29 days

- Time to weaning in supplemental oxygen

- Proportion without O2 requirement at D8, D15 and D29

e) Non-invasive ventilation, high-flow oxygen

*-* Non-invasive ventilation/high flow oxygen use up to Day 29

- Incidence and duration of non-invasive ventilation or high flow oxygen use during the study

- Time to first day with non-invasive ventilation/high flow oxygen

f) Invasive mechanical ventilation / Extra Corporeal Membrane Oxygenation (ECMO)

- Ventilator / ECMO use up to Day 29

- Incidence and duration of new mechanical ventilation or ECMO use during the study

- Time to first day with Invasive Mechanical Ventilation / extracorporeal membrane oxygenation

g) Transfer to ICU by Day 29

h) Hospitalization

- Hospital length of stay (in days)

i) Mortality

- Mortality rate at day 15 and at Day 29 and at Day 60

j)Thrombotic events

-°cumulative incidence of thrombotic events : venous, pulmonary embolism, arterial thrombotic events.

**Safety of XAV-19**

Evaluate the safety of the intervention through 29 days and 60 days of follow up as compared to the control group as assessed by:

- The cumulative incidence of SAE
- The cumulative incidence of grade 3 or 4 AE
- Proportion of discontinuations or temporary suspensions of infusion (for any reason)
- Changes in white cell count, hemoglobin, platelets, creatinine, ALT, AST, over time
- The cumulative incidence of major or opportunistic bacterial or fungal infections
- The cumulative incidence of hypersensitivity reactions and infusion reactions

**Exploratory analysis on a subset of patients**

- Change in SARS-CoV-2 status (positive or negative, and quantitatively, including variant information by sequencing) viral load over time
- Time to RT-PCR virus negativity in nasopharyngeal swab samples over 29 days

### Secondary endpoint(s)

**The key secondary endpoints are the**:

Proportion of patients who die, develop respiratory failure, as defined by the requirement of noninvasive ventilation, high-flow oxygen devices or invasive mechanical ventilation at Day 8 and Day 29.

**The other secondary endpoints are:**

1. National Early Warning Score (NEWS) assessed while hospitalized and on Day 15 and Day 29
2. Clinical status using the 8-point ordinal scale assessed daily ~~during hospitalization~~ until Day 29
3. Temperature and blood analysis between baseline and Day 15, and Day 29
4. Days of oxygen therapy over 29 days

PaO2 / FiO2 at baseline, Day 5, Day 8, Day 15, Day 29 if available

1. Days of non-invasive ventilation or high flow oxygen (if applicable) up to Day 29
2. Days of invasive mechanical ventilation/ECMO (if applicable) up to Day 29
3. Transfer in ICU
4. Hospital length of stay (in days)
5. All-cause mortality evaluated between baseline and Day 15 and between baseline and at Day 29 and at Day 60
6. Thrombotic events (peripheral venous, pulmonary, arterial)

